### Data analysis

Our main hypothesis is that TCD is as sensitive as SPECT to differentiate PD from other parkinsonian disorders. For the power analyses we assumed a sensitivity of SPECT of 90%, based on the analysis of our own data on 248 consecutive patients [19]. Assuming this 90% for TCD sensitivity we can accept as lowest border of the 95% confidence interval, 86% or higher:

*SD *= (√ (p1 (1-p1))/n → p1 = 0.9, sd 0.02, implying n = 190 patients, needed who have the hyperintensity of SN with TCD scanning.

In our pilot study 15% of the patients had an insufficient temporal bone window, so 224 patients are needed to compensate for the amount of inconclusive TCDs [28]. Based on this study we expect that 90% of all patients with inconclusive parkinsonism will ultimately have PD, so we set a target of initial 250 patients with unclear parkinsonism needed for this trial. We will calculate the sensitivity and specificity, positive predictive value, negative predictive value and diagnostic odd's ratio (OR) with its 95% confidence intervals (95% CI) of the first clinical judgment, TCD, FP-CIT SPECT scan and smell tests to predict the clinical diagnosis after 2 year follow-up. Accuracy is determined for all parkinsonian subgroups separately (PD versus APS, PD versus ET, and PD versus VP, PD versus DIP, and PD versus all other types of parkinsonism). For expected SPECT, TCD and smell tests scores for each parkinsonian disorder, see table 1.

**Table 1 T1:** Expected TCE, FP-CIT SPECT and odour recognition results for all parkinsonian disorders

Disease	FP-CIT SPECT abnormal, [19, 46]	abnormal SN TCD [47]	odour recognition deficit	cognition deficit
IPD	++	+++	+++	±
ET	Normal	normal	normal	normal
VP	normal *	normal	normal (?)	±
DIP **	normal (+)	normal (+)	normal (+)	normal (±)
MSA	++	±	+	±
PSP	++	± (?)	normal (±)	++

= normal FP-CIT tracer binding ratios

↓: FP-CIT binding of at least 2 sd. below healthy controls

* especially visual judgement together with CT or MRI

** At least 10% percent of the patients with DIP will develop to the PD [48]. So some patients in early stages of PD can theoretically present as DIP. Berg et al. investigated the relation between echointensity of SN on TCD and DIP after the start of antipsychotic drugs. Patients with serious parkinsonism scored higher echointensity as patients with mild or no parkinsonism [47].

*** In our retrospective trial 76% of the 27 patients with APS had FP-CIT binding lower as 2 standard deviations below healthy controls. In the 11 studies included in our meta-analysis this percentage varies form 67 to 100% [19, 46]

Additionally we will determine the predictive value of TCD compatible with PD for an abnormal FP-CIT SPECT scan. Finally the inter-observer reliability for SN and RN judgement by TCD will be determined (Cohen's kappa test).

SPSS 11.0 for windows (SPSS, Chicago, IL, USA) and StataSE9 (Stata corporation, Texas, USA) will be used for statistical analysis.

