## Abstract

**Background:**

Parkinson's disease (PD) is the second most common neurodegenerative disorder. As there is no definitive diagnostic test, its diagnosis is based on clinical criteria. Recently transcranial duplex scanning (TCD) of the substantia nigra in the brainstem has been proposed as an instrument to diagnose PD. We and others have found that TCD scanning of substantia nigra duplex is a relatively accurate diagnostic instrument in patients with parkinsonian symptoms. However, all studies on TCD so far have involved well-defined, later-stage PD patients, which will obviously lead to an overestimate of the diagnostic accuracy of TCD.

We have therefore set out to conduct a prospective study testing the diagnostic accuracy of TCD in patients with a parkinsonism of unclear origin.

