## Discussion

The hitherto published literature on TCD in parkinsonian syndromes are cross-sectional studies on clinically well-defined patient populations [20-30,45]. Although one has to start with these to study the diagnostic potential of a new technique, these kind of studies are obviously not representative of the clinical problem that one wants to solve with a TCD in parkinsonian syndromes. The treating neurologist wants a diagnostic tool that provides additional information in patients with a clinically indefinable parkinsonian syndrome.

The above described observational longitudinal study was designed to explicitly study this aspect in the diagnostic process. We arbitrarily choose the clinical diagnosis after two years as the surrogate gold standard. This is, of course, not ideal, as there will always remain a small proportion of patients that is not definitely diagnosable after two years, and misdiagnoses (as opposed to the ultimate gold standard the post-mortem pathological analysis) are still possible. In an effort to tackle his last obstacle we require the final diagnosis to be shared by two independent, blinded, experienced movement disorders specialist neurologists.

We included SPECT scans in the study to enable us to make a direct comparison between SPECT and TCD as to their diagnostic accuracy. Although the use of SPECT scans in the diagnostic work-up of parkinsonian patients is still debated, it is widely used [8,19,46]. We feel that this will add to the clinical relevancy of our study results. Additionally, contributions of tests for smell, depression, cognition, in the diagnostic process can be assessed also.

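### The main hypothesis compares TCD with SPECT, but the acceptance limit and sample size given for it concern TCD alone, and the calculation called a power analysis has no power term

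*Protocol article*

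**What the plan says.** The Data analysis section of the protocol article opens with a comparison of two tests: "Our main hypothesis is that TCD is as sensitive as SPECT to differentiate PD from other parkinsonian disorders".

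The sizing follows. SPECT enters as a constant: "For the power analyses we assumed a sensitivity of SPECT of 90%, based on the analysis of our own data on 248 consecutive patients". TCD is given the same value and an acceptance limit: "Assuming this 90% for TCD sensitivity we can accept as lowest border of the 95% confidence interval, 86% or higher". The resulting number is "p1 = 0.9, sd 0.02, implying n = 190 patients, needed who have the hyperintensity of SN with TCD scanning". It is then inflated for poor bone windows ("In our pilot study 15% of the patients had an insufficient temporal bone window, so 224 patients are needed to compensate") and for an expected 90% of patients with final PD, to a target of 250.

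The listed analyses are the accuracy measures of each test against the two-year diagnosis with 95% intervals, the predictive value of TCD for an abnormal SPECT, and inter-observer kappa. The Methods section schedules TCD and SPECT for every subject, and the Discussion says: "We included SPECT scans in the study to enable us to make a direct comparison between SPECT and TCD as to their diagnostic accuracy".

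**The concern.** The hypothesis concerns the difference between two sensitivities measured in the same patients. The limit and the sample size concern one sensitivity set against a fixed number. The SPECT sensitivity observed in this trial, its sampling error and the rate at which the two tests disagree play no part in either.

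A fixed benchmark is fragile here by the protocol's own reasoning. Its abstract says that earlier TCD studies used well-defined, later-stage patients, "which will obviously lead to an overestimate of the diagnostic accuracy of TCD", and this trial deliberately enrols unclear cases. Sensitivity may therefore differ from 90% for either test, and in that case only an internal comparison answers the question asked.

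The sizing is also presented as a power analysis, but it only places a confidence limit where it is expected to fall. It says nothing about the chance of meeting the limit.

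**Working it through.** **Inputs (Data analysis section).** Assumed sensitivity 0.90 for both tests; SD (a standard error) 0.02; lower 95% limit 0.86; n = 190; 15% inadequate bone window; 90% final PD; target 250. The sidedness of the interval is not stated, so two-sided is assumed. The 190 is read as PD patients with a conclusive TCD, because PD patients are the denominator of sensitivity.

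**1. The plan's own figure.** Its formula is SE = √(p(1−p)/n), so n = p(1−p)/SE².
- n = 0.9 × 0.1 / 0.02² = 225, not 190.
- A half-width of 0.04 gives 217 (z = 1.96), 225 (z = 2) or 153 (one-sided, z = 1.645). None of these is 190.
- At n = 190, SE = √(0.09/190) = 0.0218, and the expected lower limit is 0.90 − 1.96 × 0.0218 = 0.857, below the plan's 0.86.
- The later steps reproduce: 190/0.85 = 224 and 224/0.90 = 249, about 250. Starting from 225, the same steps give 225/0.85/0.90 = 294.
- Working forward, 250 × 0.85 × 0.90 = 191 evaluable PD patients.

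**2. Chance that the lower limit reaches 86% when true TCD sensitivity is 90%** (exact binomial, two-sided 95% limit).

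| n | Wald | Wilson or exact |
|---|---|---|
| 190 | 46% (at least 172 positive) | 37% (at least 173) |
| 191 | 46% (at least 173) | 36% (at least 174) |
| 225 | 51% (at least 203) | 42% (at least 204) |

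The threshold sits at or slightly above the expected lower limit, so the chance is near or below one half. The slip from 225 to 190 explains only part of the shortfall.

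**3. What the limit would do if used to judge the hypothesis** (n = 191). The true SPECT value does not enter the calculation.

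| True TCD | True SPECT | As sensitive? | Limit met, Wald | Limit met, exact |
|---|---|---|---|---|
| 85% | 85% | yes | 1.6% | 0.9% |
| 80% | 80% | yes | about 0% | about 0% |
| 92% | 97% | no, 5 points lower | 81% | 73% |

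**4. What the design gives for the paired difference.** Take equal true sensitivities and let d be the proportion of PD patients in whom the two tests disagree. Then SE = √(d/191), half-width = 1.96 × SE, and power for a margin of 4 points = Φ(0.04/SE − 1.96). The document gives no value for d, so 6% to 18% is assumed. The upper end is what independent errors at 90% would give: 2 × 0.9 × 0.1 = 0.18.

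| d | SE | Half-width | Power, 4-point margin |
|---|---|---|---|
| 6% | 0.0177 | 3.5 points | 62% |
| 10% | 0.0229 | 4.5 points | 42% |
| 18% | 0.0307 | 6.0 points | 26% |

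The 4 points are illustrative (90 minus 86).

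**The case against.** The strongest reply is that the 86% appears only in the sizing text. No sentence says that TCD will be declared as sensitive as SPECT once its limit reaches 86%. SPECT sensitivity will also be estimated, with its own interval, in the same patients, and a condensed article may leave a paired test to an analysis plan that is not shown. All of this stands. A reader might infer that the plan formally tests TCD against 86%, but the document does not say so, and the results in step 3 of the working are conditional on using the limit that way. What remains is that the article does fix a limit and a sample size for its main hypothesis, and both address a different question. A later paired test would not turn a one-sample precision formula into a justification for 250 patients.

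Three further inferences would go too far:
- **That the 90% for SPECT comes from an unrepresentative series.** The Background section criticises many SPECT studies for their case mix, but the 90% comes from the authors' own consecutive patients. Nothing shown says that this series shares the fault.
- **That power is below 50% on any reading.** A one-sided 95% Wald limit at n = 190 is met in about 56% of trials, and about one half is inherent in any precision-based sizing.
- **That the plan sets a 4-point non-inferiority margin.** The 4 points are the distance from an expected estimate to its confidence limit. No margin on the difference is stated.

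**Conclusion.** The concern holds in this form: a comparative main hypothesis is paired with a limit and a sample size for TCD alone, no contrast of the two sensitivities is listed, and the calculation called a power analysis contains no power. Under the plan's own assumptions and a two-sided 95% interval, the limit is reached in 36–46% of trials with about 190 evaluable PD patients. The stated inputs give 225 rather than 190, and correcting this raises the chance only to 42–51%.

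If the limit were used to decide, it could reject a true hypothesis (under 2% success with both tests at 85%) and accept a false one (73–81% success with TCD 5 points lower). The paired precision and power figures rest on an assumed discordance and an illustrative margin; at 6% to 18% discordance, power for 4 points stays below 80%. Final diagnoses on which the two specialists disagree are coded inconclusive and are not allowed for in the sizing, so the evaluable number may be lower still.

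**What to change.** Make the primary analysis the paired difference in sensitivity, TCD minus SPECT, among patients with a final diagnosis of PD and both tests conclusive. Report it with a score-type 95% interval for paired proportions. Claim that TCD is as sensitive only if the lower limit lies above a margin that the sponsor states in advance. Do not use McNemar's test to support that claim: it tests equality, and a non-significant result does not show non-inferiority.

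Keep the enrolment target, correct the 190, and replace the power paragraph with what the design delivers: about 191 evaluable PD patients, a half-width of about 3.5 to 6.0 points for the difference over an assumed discordance of 6% to 18%, and the power for the chosen margin (about 62% down to 26% if it were 4 points). Keep the separate accuracy figures for each test as descriptive results.

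The cost is a change of wording and a less favourable stated precision or power. Both tests are already scheduled for every patient, so no new procedure is needed.

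### The planning figure of 190 does not follow from its stated inputs, which give 217 to 225; 250 enrolled narrowly misses the 86% lower limit, and the 190 are also mislabelled

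*Protocol article*

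**What the plan says.** All of this stands in the Data analysis section of the protocol article.

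- The hypothesis concerns sensitivity: "Our main hypothesis is that TCD is as sensitive as SPECT to differentiate PD from other parkinsonian disorders".
- The precision target is: "Assuming this 90% for TCD sensitivity we can accept as lowest border of the 95% confidence interval, 86% or higher".
- The calculation uses the standard error of a single proportion (written as SD), with an expected proportion of 0.9, and concludes: "sd 0.02, implying n = 190 patients, needed who have the hyperintensity of SN with TCD scanning".
- An allowance for the 15% with an insufficient bone window follows: "so 224 patients are needed to compensate for the amount of inconclusive TCDs".
- A further allowance, because 90% of those enrolled are expected to turn out to have PD, leads to the target of 250.

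**The concern.** The formula, both inputs and the result are printed together, and they do not agree. The result is then carried into the enrolment target, which is the only justification of size in the article. If 190 is too small for the stated criterion, the article claims slightly better precision than the design is expected to give.

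There is also a problem of definition. Sensitivity is a proportion among patients who have the disease. The text attaches the required number to patients with a positive TCD, which is a different group from the one the hypothesis needs.

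**Working it through.** **Inputs, all from the Data analysis section:** expected sensitivity p = 0.90; SE = 0.02; lower 95% limit of at least 0.86, so a half-width of 0.04; 15% unreadable TCD; 90% with a final diagnosis of PD; 250 enrolled. Whether the limit is one-sided or two-sided is not stated, and two-sided is taken as the default.

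**1. The plan's own figure.** With SE = √(p(1 − p)/n), n = p(1 − p)/SE² = 0.09/0.0004 = **225**, not 190. (The bracket as printed puts n outside the root, which would give 0.3/0.02 = 15. That is clearly not meant and is not counted as an error here.)

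**2. Other routes to 190.**

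| Reading | n |
|---|---|
| Two-sided, 1.96 × SE = 0.04 | 216.1, so 217 |
| One-sided, 1.645 × SE = 0.04 | 152.2, so 153 |
| Variance taken at 0.86, one-sided | 204 |
| Variance taken at 0.86, two-sided | 289.1, so 290 |
| Arcsine scale | 252 |
| Logit scale | 293 |
| Wilson lower limit of at least 0.86 | 290 |
| Exact lower limit of at least 0.86 | 296 |

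None gives 190. Working back, n = 190 corresponds to SE = √(0.09/190) = 0.0218.

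**3. The later steps do follow from 190.** 190/0.85 = 223.5, stated as 224. Then 223.5/0.90 = 248.4, rounded up to 250. So 190 is the figure on which the enrolment target was built, and not a misprint for 225.

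**4. Enrolment that the criterion needs, with the same allowances.**

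- From 217: 217/0.85/0.90 = 283.7, so 284.
- From 225: 225/0.85/0.90 = 294.1, so 295.

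This is 34 to 45 more than 250, or 14% to 18%.

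**5. What 250 enrolled gives.** 250 × 0.85 × 0.90 = 191.25, about 191 patients with final PD and a readable TCD. At an observed 90%, SE = √(0.09/191) = 0.0217, or 2.2 points.

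- Normal approximation: 0.90 − 1.96 × 0.0217 = 0.857 and 0.90 + 1.96 × 0.0217 = 0.943. The lower limit is about 0.3 points short of 86%.
- Wilson: lower limit 84.9%. Exact: 84.8%. With a whole count of 172/191 (90.05%) these become 85.0% and 84.9%, with upper limits of 93.5% and 93.9%.

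**6. The label.** Dividing by the 90% expected to have PD makes sense only if the 190 are PD patients, and dividing by 0.85 only if they have a readable TCD. The arithmetic therefore already uses the right denominator, and the descriptive phrase contradicts it.

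**The case against.** The strongest defence is rounding. The SE is printed to one significant figure and the limit to a whole percent. At n = 190 the SE of 0.0218 prints as 0.02 and the lower limit of 85.7% prints as 86%. If 86% is read to the nearest percent (85.5% or above), 171 evaluable patients suffice (0.09 × (1.96/0.045)² = 170.7). That is about 224 enrolled, and 250 exceeds it.

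This shows that the discrepancy is small, but it does not rescue the derivation. An SE that prints as 0.02 lies between 0.015 and 0.025, which fits any n from 0.09/0.025² = 144 to 0.09/0.015² = 400. It cannot imply 190 in particular. The criterion is also worded as a minimum, "we can accept as lowest border of the 95% confidence interval, 86% or higher", and 85.7% is below it. A one-sided limit at n = 190 would be 86.4% and would meet the criterion, but that reading needs only 153 patients and so does not explain 190 either.

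Two parts of the defence do stand. First, on the protocol's own formula the shortfall is only about 0.3 points. The gap of about 1 point appears only with Wilson or exact limits, and the article does not commit to either. Second, the intervals will be reported with the results, so readers will see the precision actually achieved.

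A reader might also infer that the wrong denominator caused the shortfall, or that the study was really sized for a positive predictive value. The documents do not support either. The later divisions treat the 190 as PD patients with a readable TCD, so the label changes no number.

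**Conclusion.** The calculation is wrong as written. The stated inputs give 225, or 217 with 1.96, and the figures of 224 and 250 inherit the error. Under the protocol's own allowances the stated criterion needs about 284 to 295 enrolled. With 250, the expected two-sided lower limit at 90% observed sensitivity is 85.7% by the normal approximation, or about 84.9% by Wilson or exact limits. The mislabelled denominator is a separate error of wording with no numerical effect.

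It would go too far to conclude that the study is materially too small or must enrol 295. The miss is a fraction of a point on the protocol's own method, and 295 is only the upper of the two normal-approximation figures.

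These results assume 90% sensitivity, 15% unreadable TCD, 90% final PD and a two-sided 95% interval. They make no allowance for patients whose final diagnosis is coded inconclusive because the two specialists disagree (section E, Re-examination at two-year follow-up). The article gives no rate for this, and any such loss would lower the precision further.

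**What to change.** In the Data analysis section:

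- Correct the calculation: p = 0.9 with SE = 0.02 gives 225; setting 1.96 × SE = 0.04 gives 217.
- State what 250 enrolled is expected to give: about 191 patients with a final diagnosis of PD and a readable TCD, a standard error of 2.2 points, and at 90% observed sensitivity a 95% CI of about 86% to 94% (normal approximation, lower limit 85.7%) or 85% to 94% (Wilson or exact). Name the interval method used.
- Drop the 86% minimum, or keep it and state the enrolment it requires (about 284 to 295 on the normal approximation).
- Describe the required number as patients with a final diagnosis of PD and a readable TCD, in place of patients with a hyperintense substantia nigra.

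The cost is wording only. No extra patients are needed if the precision is restated, and the claimed precision becomes slightly less favourable. Keeping the 86% minimum as a design requirement would cost 34 to 45 more patients.

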### B. SPECT

All subjects will undergo SPECT scanning within 6 weeks of inclusion in the study. In this study FP-CIT (^123^I-ioflupane, Nycomed, Amersham, U.K.) is used as presynaptic radiotracer. Medication (amphetamine, citalopram, fentanyl, cocaine, fluoxetine, fluvoxamine, paroxetine, sertraline, venlafaxine) which could interfere with the radiotracer is discontinued at least 5 half life times. After intravenous injection of the tracer, SPECT measures baseline dopamine transporter integrity in the brain. SPECT is performed with a triple head camera (MultiSPECT3, Siemens, Ohio, USA) equipped with high-resolution collimators. A semi-automatic template model programme is used to calculate the ratios between left striatal and right striatal and occipital regions respectively. Total time of acquisition is 30 minutes (45 seconds per frame for 40 views per detector). Zoom factor: 1.00 and the matrix size: 128 × 128. Filtered back-projection acquisition is performed. Images are filtered using a Butterworth filter with a cut-off value of: 0.4–0.5 and an order of 5. A division between the caudate nucleus and putamen is made. The ratios are corrected using Alderson's brain phantom, with known activities in the caudate nucleus and putamen. A binding of two standard deviations below healthy controls is considered as abnormal (FP-CIT 8.25 +-1.85 for putamen and 7.76 +-1.77 for caudate nucleus). Beside quantitative the scans will be also judged visually by the same nuclear specialist blinded for the final clinical diagnosis. If quantitative and visual judgments do not agree the conclusion of visual judgment is taken (unpublished data).

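### The 90% TCD sensitivity and its 86% limit refer to readable scans only, so equality with SPECT could be concluded without qualification when it does not hold in all enrolled PD patients

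*Protocol article*

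**What the plan says.** All places are in the Protocol article.

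- **Data analysis, hypothesis.** "Our main hypothesis is that TCD is as sensitive as SPECT to differentiate PD from other parkinsonian disorders".
- **Data analysis, planning values.** "For the power analyses we assumed a sensitivity of SPECT of 90" per cent, and for TCD "Assuming this 90% for TCD sensitivity we can accept as lowest border of the 95% confidence interval, 86% or higher". The base number follows: "sd 0.02, implying n = 190 patients, needed who have the hyperintensity of SN with TCD scanning".
- **Data analysis, allowance for unreadable scans.** In the pilot, "15% of the patients had an insufficient temporal bone window, so 224 patients are needed to compensate for the amount of inconclusive TCDs". A last step reaches the target of 250 because "we expect that 90% of all patients with inconclusive parkinsonism will ultimately have PD".
- **Section C (TCD).** The substantia nigra is read in three categories. A poor bone window leads to the inconclusive category, which is separate from a negative reading.
- **Section B (SPECT).** Every participant is to be scanned. "If quantitative and visual judgments do not agree the conclusion of visual judgment is taken". No inconclusive category is listed for SPECT.
- **Data analysis, planned measures.** Sensitivity, specificity, predictive values and odds ratio are listed with confidence intervals. The text does not say which patients form the denominator for TCD, for SPECT or for their comparison.
- **Discussion, purpose.** "The treating neurologist wants a diagnostic tool that provides additional information in patients with a clinically indefinable parkinsonian syndrome". The same section promises a direct comparison of the two tests.

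**The concern.** Enrolling more patients to make up for unreadable scans makes sense only if those patients stand outside the denominator of TCD sensitivity. Had they been counted as PD not detected, they would have stayed in it, no inflation would have been needed, and 90% could not have been the planning value.

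The study is therefore sized and judged on TCD among patients whose bone window allows a reading, whereas the hypothesis is worded for PD patients in general. Extra recruitment gives the readable-scan estimate the intended precision but does not change whom it describes.

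At stake is the headline conclusion. The trial could report that TCD matches SPECT while a sizeable share of enrolled PD patients gets no usable TCD answer. The Abstract faults earlier TCD studies for overestimating accuracy through their choice of patients. Leaving out patients who cannot be imaged also selects in TCD's favour.

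**Working it through.** **Inputs** (all from Data analysis): 190 base patients; 15% insufficient window in the pilot; 90% of patients expected to have PD; 90% sensitivity assumed for SPECT and for TCD; 86% lower limit; target 250. I take 190 as given, since its derivation is a separate matter.

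**1. Reproduce the plan's figures.**
- 190 / (1 − 0.15) = 223.5, so 224, as stated.
- 224 / 0.90 = 248.9, so 249, in line with the stated 250.
- With 190 readable scans at 90%: SE = √(0.90 × 0.10 / 190) = 0.0218, and 0.90 − 1.96 × 0.0218 = 85.7%, close to the 86% limit.

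The limit is thus met, near enough, on 190 readable patients. This confirms that the 90% and the 86% belong to readable scans.

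**2. Carry the same figures to all PD patients.**
- PD patients: 250 × 0.90 = 225.
- Readable: 225 × 0.85 = 191. Unreadable: about 34.
- Detected at 90% of readable: 191.25 × 0.90 = 172.
- Among readable patients: 90%. Among all PD patients: 0.90 × 0.85 = 76.5% (Wilson 95% CI 70.5% to 81.6%).

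**3. Vary the unreadable share f.** The 15% is one pilot percentage, so the other rows are assumed values.

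| f | All-PD sensitivity, 0.90 × (1 − f) | Ceiling if every readable PD scan is positive, 1 − f |
|---|---|---|
| 5% | 85.5% | 95% |
| 10% | 81.0% | 90% |
| 15% | 76.5% | 85% |
| 20% | 72.0% | 80% |

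With 90% among readable scans, even the all-PD point estimate reaches 86% only if f is at most 1 − 0.86/0.90 = 4.4%. The ceiling falls below 86% once f exceeds 14%.

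**4. Compare with SPECT at its assumed 90%.** The SPECT denominator is not stated, so take both possibilities.
- *SPECT in all 225 PD patients.* Difference 0.90 − 0.765 = 13.5 points. If the tests are independent given PD (an assumption), the discordant proportions are 0.765 × 0.10 = 0.0765 and 0.235 × 0.90 = 0.2115. SE = √((0.0765 + 0.2115 − 0.135²)/225) = 0.0346, 95% CI 6.7 to 20.3 points.
- *SPECT in readable patients only.* 90% against 90%, no difference. About 34 of 225 PD patients still have no TCD answer, and the comparison says nothing about them.

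**The case against.** **This is only a recruitment step.** The article gives no analysis rule for inconclusive TCDs, and a condensed article may leave that rule to a fuller document. It stands that exclusion is inferred and not written, and silence alone would not be a finding. But the plan is not silent on its basis: it adopts replacement and builds both the sample size and the acceptance limit on it. A later rule counting unreadable scans as misses would no longer fit the 90% and 86%.

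**Sensitivity among interpretable scans is a legitimate quantity.** It is, when labelled as such and reported with the failure rate. An inconclusive result is also not a negative one: the neurologist sees no answer and can turn to other information. Counting it as not detected is the strict convention, which is why both figures are needed. The fault lies in a hypothesis that carries no such label.

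**A reader might infer that SPECT counts every patient, so that the two sensitivities rest on different people.** The document does not say so. It plans SPECT for everyone and lets the visual read settle disagreement, but it states no SPECT denominator, says nothing on failed scans, and does not rule out a comparison restricted to patients with both results. The concern does not depend on this.

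**A reader might infer that TCD can never detect more than 85% of PD patients.** That is too strong. The figure applies one pilot percentage to PD patients in a new population. Its denominator is unclear: the Background describes a pilot of 45 patients, while Data analysis cites a different reference. At 10% unreadable the ceiling is 90%, above the 86% limit. Atypical configurations also count as inconclusive and could raise the loss. The second reader's off-line scoring may change it, although it uses images from the same examination.

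**The counts are idealised.** The 225 ignores patients whose two-year diagnosis is coded inconclusive, and the 13.5-point interval needs the independence assumption. Both affect the counts and the interval, not the product 0.90 × 0.85.

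**Conclusion.** The point holds in limited form. By inflating for unreadable windows, the plan implies that its 90% and 86% describe readable scans, while its main hypothesis is stated without that restriction. If the pilot's 15% applies to PD patients here and readable sensitivity is 90%, TCD detects 76.5% of all PD patients, or 81% to 72% over an assumed 10% to 20% unreadable. Equality with SPECT could then be concluded among readable patients when it does not hold among all enrolled PD patients.

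The document supports neither a claim of unequal denominators for the two tests nor a fixed 85% limit on TCD. No data are lost: window quality and inconclusive readings are recorded per patient, and SPECT is planned for all. The matter should still be settled before results are known, because it decides how the main conclusion may be worded.

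**What to change.** Add to Data analysis that TCD and SPECT sensitivity are compared on the same patients in two sets:

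1. All patients with a final PD diagnosis, an unreadable TCD or a failed SPECT counting as PD not detected.
2. Patients with readable results on both tests.

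Also:
- Report the unreadable share with its 95% CI, overall and by final diagnosis.
- For specificity, give the readable-only figure and an all-patient figure in which unreadable results appear as a separate row and are not credited as true negatives.
- If only set 2 supports equality, restrict the conclusion to patients with an adequate bone window.

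The cost is a few sentences and one extra table, with no new patients or data. The downside for the sponsor is a less favourable all-patient TCD figure (about 76.5% instead of 90% on the plan's own values) and probably a qualified conclusion.
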